#### Sample size

Our proposed sample size includes 10 clusters with an average cluster size of 32 participants, consistent with the range reported in pilot cluster randomized controlled trials (inter-quartile range: 4–16 clusters; cluster size: 14–82) [60]. This sample size is appropriate for a pilot study designed to assess the feasibility and acceptability of implementing the intervention at the school level as primary and to estimate the variability in key implementation outcomes such as fidelity and student outcomes as secondary. This sample size also reflects the available resources for the pilot study while still allowing for meaningful data collection.

The justification for this sample size aligns with best practices for pilot studies, which prioritize achieving sufficient precision for key implementation parameters rather than powering analyses for statistical significance [52]. Given the exploratory nature of pilot studies, formal power calculations are not required, as the primary aim is to assess feasibility, variability, and implementation processes [61]. To ensure that our pilot sample will allow us to draw reasonable conclusions for the parameter estimates in a larger study, we conducted an AIPE (Accuracy in Parameter Estimation) analysis. We found that across 1000 simulations, the average 95% confidence interval widths for the student outcomes were 0.18 standardized units, and 0.85 for school-level variability. The focus on AIPE is more central to our aim in this pilot study than statistical power, especially for the school-level effects. Thus, our proposed sample size reflects a balance between the pragmatic constraints of a pilot trial and the need to collect adequate data to inform the design and conduct of subsequent larger-scale effectiveness trials.

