#### Eligibility and randomization

We will focus on schools that could most benefit from RAPD by employing the following screening criteria: schools must include seventh-grade education level; health teachers must report delivering less than 80% of the MMH curriculum (the state-identified fidelity standard) and/or report two or more barriers to MMH implementation (see “Measures”). These criteria are adapted from a previous school-based study and informed by study partners and the study team's previous research on MMH implementation [62, 63]. Five of the matched sites will be randomized to the RAPD and five to standard implementation: the MMH curriculum manual, training, and technical assistance. Research team members will use the GenRandGroups function within the DescTools package (version 0.99.54) in R. The randomization procedure is designed to pilot methods to ensure balanced participant allocation across experimental conditions. Schools will be the randomization unit, with matching criteria for assigning schools to treatment groups involving factors such as school size, the percentage of students eligible for free/reduced lunch, and the health coordinator serving the school. Participants (schools) were not masked as is not practical or desired in this implementation study, which focuses on improving the speed, quality, and quantity of intervention delivery through different strategies, acknowledging the influence of participants' awareness on observable outcomes. The health coordinators have successfully recruited schools for previous similar studies [63, 64]. All standard implementation sites will receive RAPD following the trial portion of the study. We focus on middle school because of the heightened risk for drug use initiation during this developmental period [65].

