#### Student outcomes

Secondary outcomes at the student level are summarized in Table 2. Student surveys will be administered at baseline (the beginning of the semester or trimester), when the student is in health class, and after delivery of the drug use prevention units (post-test). During the school year, participating teachers will administer the pre-/post surveys for each cohort of students if they teach health for more than one term/year.

**Table 2 Tab2:** Secondary study measures student level

Student-level outcomes			
**Construct (# items)**	**Scaling**	**Timing**	**Source**

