#### Student data

Aim 2 analyses of student survey data will focus on estimates of effect size, variance, implications for statistical power, and exploring potential differences between the RAPD implementation strategy and standard implementation on student perceptions of risk, attitudes, behaviors, and MMH engagement. Given the study design, we will utilize mixed-factorial statistical analyses to characterize the magnitude of differences of the pre-/post changes in measures of risk, attitudes, beliefs, and other student-level outcomes. Each model will utilize random Y-intercepts to accommodate the repeated observations within student and school, and fixed-effects parameters comparing time (pre-/post changes), group (RAPD, standard implementation difference), sex/gender, socioeconomic status, and their interaction (as appropriate given sample size constraints). We will employ mixed-factorial regression models for outcomes assumed to follow a normal distribution, logistic regression for dichotomous outcomes, or ordinal regression for outcomes ordinal in scale. The analyses will use Satterthwaite corrections for degrees of freedom.

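### For student outcomes measured before and after delivery, random intercepts alone leave school-level differences in change out of the RAPD-by-time interval, so it is too narrow if schools change differently

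*Protocol article*

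**What the plan says.** Under Student data, the article sets out to "characterize the magnitude of differences of the pre-/post changes in measures of risk, attitudes, beliefs, and other student-level outcomes". The fixed part of the model has "fixed-effects parameters comparing time (pre-/post changes), group (RAPD, standard implementation difference), sex/gender, socioeconomic status, and their interaction". The random part is fixed for every model: "Each model will utilize random Y-intercepts to accommodate the repeated observations within student and school". The small-sample provision is one sentence: "The analyses will use Satterthwaite corrections for degrees of freedom".

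Under Eligibility and randomization, "Schools will be the randomization unit", and "Five of the matched sites will be randomized to the RAPD and five to standard implementation". The Sample size section plans "10 clusters with an average cluster size of 32 participants". The Student outcomes section adds that "participating teachers will administer the pre-/post surveys for each cohort of students if they teach health for more than one term/year", so one school may contribute several cohorts.

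Table 2 gives the timing. Risk perception and drug use are measured before and after implementation; satisfaction and key skills are measured only afterwards. The article names no school-by-time effect, school-level slope for time, cluster-robust variance or school-level analysis.

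**The concern.** RAPD is given to whole schools and works through teachers and coordinators. Schools can therefore differ in how much their students change over a term, for reasons unrelated to arm. That variation is part of the error of a comparison of five schools with five. A school intercept that is the same at both surveys describes differences in level, not in change.

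Two things are at stake. First, the intervals for the RAPD-by-time effect may claim more precision than ten schools can give. Second, the student analyses are meant to supply effect sizes, variances and power considerations for a larger cluster trial. The between-school variance of change, which a trial analysing change needs for sizing, is not estimated by this model.

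**Working it through.** **The plan's own precision figure.** The Sample size section reports an average 95% interval width of 0.18 standardized units for student outcomes. It does not give the target parameter, ICC, correlation or model, so 0.18 cannot be strictly reproduced. Ignoring school-level change, with student pre/post correlation r and N students:

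- Overall pre/post change: width = 2 × 1.96 × √(2(1−r)/N). This equals 0.18 at r = 0.75, 0.66 or 0.53 for N = 240, 320 or 450.
- RAPD-by-time contrast: width = 2 × 1.96 × 2 × √(2(1−r)/N). This equals 0.18 only at r = 0.94, 0.92 or 0.88.

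The three N values are 10 schools at 24 students (Aim 2, Sample and setting), 10 at 32 (Sample size), and the 450 expected survey participants (Pilot study procedures), which is 45 per school.

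**Why the intercepts cancel.** Write a student's score as fixed part + school intercept + student intercept + residual. Post minus pre removes both intercepts. With balanced, complete data the time-by-group term is then a student-level comparison of change scores on 10m − 2 df: 238, 318 or 448 for m = 24, 32 or 45. In 20 fits of the stated linear model to simulated data, the mean standard error was 0.0982, against 0.0981 for the change-score comparison. Satterthwaite df are built from the variance components in the model, so they cannot bring this contrast back to the 8 df between schools.

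**Size in one scenario.** Assumed, not in the documents: total variance 1, ICC 0.05, school-effect pre/post correlation (CAC) 0.8, r = 0.6 within school, m = 32.

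- School variance of change: 2 × 0.05 × (1 − 0.8) = 0.020.
- Student variance of change: 2 × 0.95 × (1 − 0.6) = 0.76; divided by 32, 0.02375.
- True variance of the contrast: (2/5) × (0.020 + 0.02375) = 0.0175, so SE = 0.132.
- The model's pooled change variance picks up some school variation: 0.76 + 0.020 × (32 × 4)/159 = 0.776. SE = √(2 × 0.776/160) = 0.0985.
- SE ratio: 0.132/0.0985 = 1.34. Coverage is P(|Z| < 1.967/1.34), about 86%.
- Simulation (20,000 trials): the stated model has mean width 0.39 SD and coverage 85.8%. A school-level comparison on 8 df has mean width 0.59 SD and coverage 94.8%.

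**Range.** Coverage of the nominal 95% interval at r = 0.6:

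| ICC | CAC | m = 24 | m = 32 | m = 45 |
|---|---|---|---|---|
| 0.05 | 1.0 | 95.0% | 95.0% | 95.0% |
| 0.02 | 0.9 | 93.6% | 93.1% | 92.3% |
| 0.02 | 0.6 | 89.5% | 87.6% | 84.6% |
| 0.05 | 0.8 | 87.9% | 85.6% | 82.0% |
| 0.05 | 0.6 | 81.7% | 77.8% | 72.4% |
| 0.10 | 0.8 | 81.0% | 77.1% | 71.6% |
| 0.10 | 0.6 | 71.5% | 66.2% | 59.6% |

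A lower student correlation softens the effect. At r = 0.4, ICC 0.05, CAC 0.8 and m = 32, the variance ratio against within-student error alone is 1 + 0.020 × 32/(2 × 0.95 × 0.6) = 1.56. The SE ratio is 1.25 and non-coverage about 11.7%.

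**Planning consequence.** In the main scenario the variance of a school's mean change is 0.04375, while the model implies 0.776/32 = 0.02425. A later trial of change, sized from this model at 32 per school, would understate the number of schools by a factor of about 1.8.

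**The case against.** The strongest reply is that the effect is conditional and the setting forgiving. If every school would change alike apart from student noise, the stated interval is correct, and at low ICC and high CAC it is close to nominal. The outcomes are secondary and exploratory. The article disclaims power as its aim, and its progression criteria rest on recruitment, retention, data collection and feasibility. With balanced data the point estimate is unchanged. All of this stands and limits the severity. It does not make the stated structure right: the random effects are specified for each model, so this is not a detail left to a fuller plan.

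A reader might infer more than the documents support:

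- *That all student models are affected.* For satisfaction and key skills, measured only afterwards, the school intercept carries the between-school variance and Satterthwaite df suit the small number of schools.
- *That the intervals are certainly wrong by a known amount.* The size rests on an ICC and correlations that the article does not give.
- *That ordinal and logistic models have a further, quantified error because Satterthwaite df belong to linear models.* That depends on software and estimation method, which are not stated. The figures above are for the linear model only. If risk perception or drug use is modelled as ordinal or binary, school-by-time variance is still missing, but its effect was not computed.
- *That the 0.18 width is an error.* The article does not say it refers to the RAPD-by-time contrast.
- *That 8 df is settled.* Sites are matched before randomization. If matching is in pairs and the analysis respects it, five pairs leave 4 df.

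**Conclusion.** The point holds for the outcomes measured before and after, risk perception and drug use. In the linear model with complete, balanced data, the RAPD-by-time interval reflects within-student error on about 238 to 448 df. It leaves out school-level differences in change, although ten schools carry the randomization. The loss of coverage is conditional on a school-effect pre/post correlation below 1, which is the usual expectation for a teacher-delivered strategy but is not documented here. Under the assumed ranges it goes from barely noticeable to serious. The missing variance of change is a second loss, since informing the later trial is a stated purpose of these analyses. Severity is moderate: this should be corrected before the student data are analysed, but it does not touch the primary outcomes or the progression decision.

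**What to change.** For the pre/post student outcomes, do one of the following:

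- add a school-by-time random effect (equivalently, a school-level random slope for time), with cohort within school considered where a teacher surveys more than one term; or
- model the post score adjusted for the baseline score, with a school random intercept.

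In either case, report a comparison of school-mean changes as a check. Use between-school degrees of freedom: 8, or fewer if the analysis respects the matching. Give the same check for outcomes handled by ordinal or logistic models, and state which degrees of freedom apply there. Report the estimated between-school variance of change with its uncertainty. The post-only outcomes need no change.

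The cost is about two sentences in the analysis section and no new data. Intervals will be wider, and with ten schools the added variance component will be imprecise and may be estimated at zero, which is why the school-mean check belongs beside it.

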#### Missing data

Before data collection, the team will meet to discuss plausible reasons for missing data and determine items related to those reasons to include in the quantitative survey as auxiliary variables (i.e., variables that might lead to non-random patterns of missingness but are not of interest as part of the main hypotheses) to increase the likelihood of missing data being due to MAR (missing at random) and MCAR (missing completely at random) processes. In addition to using added items to inform future handling of missingness (i.e., multiple imputation, FIML (full information maximum likelihood)), we will calculate informative principal components [102] so our handling of missing data is informed by all available data, including multivariate interactions, without adding undue burden on model estimation stemming from a large number of variables.

### Aim 3 (exploratory aim): assess the costs and benefits of RAPD from multiple partner perspectives

#### Study design

We use an exploratory sequential mixed methods design to draw inferences about key costs and benefits that would not be feasible with one method alone (see Fig. 4) [45]. Costs are inherently dependent on the partners and decision-makers involved and the implementation context [45, 46]. We will employ this design to obtain information about costs and priorities from essential perspectives central to MMH implementation and sustainment and most relevant to the context that can inform future financing and issues of funding stability of implementation strategies, consistent with previous research [103]. Because the key costs and benefits across multiple partner perspectives are largely unknown, we use this study design to develop a costing tool tailored to the setting, making it more likely that the tool will be helpful to the participants being interviewed. This approach will advance pragmatic costing tools that account for multiple perspectives and understand implementation costs and benefits across perspectives that can support sustainment.

**Fig. 4 Fig4:**
[figure not shown]
Aim 3 exploratory sequential mixed methods design

#### Procedures

During Aim 1 focus groups, we will include questions on perceptions of costs, benefits, and priorities in implementing and sustaining the rapid responses to public health events from each partner’s perspective. Focus groups are useful when exploring perceptions of products, such as the MMH curriculum, and services, such as training or support, and their associated costs, and therefore suitable for this aim. Groups will be asked open-ended questions using a semi-structured interview guide to identify their perceptions of the costs and benefits of MMH implementation and asked to prioritize them. Focus groups will convene virtually, and we will record meetings and transcribed using an online conferencing platform. Qualitative data collection and analysis will be as described in Aim 1. Quantitative: we will develop a costing tool for partners considering implementation to estimate the net costs of using RAPD versus standard implementation through an activity-based costing (ABC) approach, considering multiple perspectives. See Table 3 for potential costs and priorities across partner groups. Consistent with emerging recommendations in the field, we will focus on costs required for replication versus research or development costs [104]. Identifying key implementation costs based on the qualitative data phase will provide practical information for partners regarding resources required for EBI delivery with high fidelity and potential advantages, from an economic perspective, of using RAPD versus standard implementation. Further, identifying costs, benefits, and priorities will also elucidate areas of synergy and conflict across perspectives as a first step in resolving potential conflicts.

**Table 3 Tab3:** Example key cost considerations for different interested parties, adapted from clinical contexts, Eisman et al. [44]

Interested party perspective	Key priorities	Example of pre-implementation costs	Example of implementation costs	Example sustainability costs
State agencies	Maximize public health impact, est. effective practices	Costs for MMH updates, review, formatting, promotion	Developing and executing health coord trainings	Review and revisions, updating assessments, committee meetings
System (i.e., regional service agency)	Stay within budget; align with the mission (education)	Capital expenses; technology upgrades,	Time costs for logistics, dissemination, training, facilitation	Time costs for updating priorities, alignment with state policies
Organization (i.e., school)	Stay within budget; meet benchmarks (education)	Substitute teacher costs, time, and space costs for updated training	Opportunity costs of time spent deploying RAPD	Costs to maintain quality implementation
Provider team: administrative staff	Effective allocation of staff/resources, meet youth/family needs	Costs of promotion and onboarding	Opportunity costs of time spent on RAPD versus other initiatives	Retraining costs; cost audit and feedback
Provider team: teachers, professionals	Improve workflow; competing demands; relative benefit	Opportunity costs for training, logistics, and implementation prep	Time required to review, incorporate updates into lessons	Opportunity costs for ongoing activities, training

### Measures

#### Qualitative

We will design a focus group guide consisting of three primary questions. Question 1 will ask participants to discuss their perceptions and experiences with the costs and resources associated with MMH implementation and who bears those costs. Question 2 will ask about resource barriers to effective implementation. Question 3 will ask participants to discuss their priorities of costs and benefits related to the MMH implementation. Using Krueger and Casey’s protocol [53], we will encourage groups to deeply explore and expand on their responses.

#### Cost identification and tracking tool

We will identify resources needed for activities during the implementation strategy deployment process, from exploration to sustainability, consistent with other implementation costing tools [104] that map activities across implementation phases based on the results from the qualitative analysis. We will prospectively collect cost data and pilot-test our costing tool. The partner groups, including health coordinators, MDHHS staff, school admin, and teachers, will track their time, other relevant costs, activities/tasks, or benefits as part of RAPD deployment. These tasks may include developing an implementation plan, training, linking to resources for curriculum updates, and technical assistance.

### Data analysis

#### Qualitative

As part of the Aim 1 data analysis, the research team will examine responses to each cost/resource-related question within each partner group, applying a code to capture similar responses. We will organize codes into themes and analyze themes to identify the frequency, extensiveness, intensity, specificity, internal consistency, and participant perception of importance for each theme. We will organize results side-by-side in tables to allow for comparison across partner groups. We will use the analysis of themes (frequency, extensiveness, intensity, consistency) to develop items for the costing tool that captures the themes in the qualitative analysis. We will use a modified Delphi technique to refine the tool and incorporate expert opinion from community partners (i.e., the health coordinators and school personnel), that is, practice-based evidence [105]; upon the first iteration of the tool, we will share it with key partners to provide additional input in advance of cost data collection.

#### Cost

We will calculate costs based on time spent by hourly wage plus fringe rates for staff using Bureau of Labor Statistics data. All costs will be adjusted to current US dollars using the Consumer Price Index [106]. We will estimate other non-labor costs based on study data (e.g., materials). We will report summary statistics, including mean costs with 95% confidence intervals.

## Discussion

### Expected outcomes

We expect Aim 1 outcomes will contribute toward identifying critical gaps in meeting population needs regarding emerging drugs and addressing health disparities in the impact of drug use in under-resourced communities. We expect Aim 2 outcomes will contribute toward designing and testing strategies for drug use prevention in real-world settings and finding ways to reduce health disparities. This includes systematically designing RAPD, that can be applied to other drugs, interventions, and urgent public health issues. We also expect that Aim 2 will result in a feasible, acceptable, and appropriate set of strategies to enhance MMH fidelity and effectiveness and provide an infrastructure for future emerging drugs. This aim will also collect data regarding deploying RAPD in schools serving low-income students, which will be critical to further refinement to enhance equity in preparation for a future large-scale type 3 hybrid trial. We also expect that students in schools receiving RAPD will report increased risk perception and higher levels of student engagement compared to those in standard implementation schools. This mixed methods research will support a subsequent, large-scale trial to address urgent and emerging drug issues among youth and address disparities in system responses. For Aim 3, we expect to develop an implementation strategy costing tool that captures vital interested party priorities and relevant costs related to adaptation to inform a comparative economic evaluation for the larger implementation trial.

